1. **Lead-in Period:** During the 1-3 week lead-in period after the baseline visit, participants will be asked to use the SnapCalorie^TM^ phone application and to complete the daily meal timing and sleep survey to log at least 7 days of their normal dietary and sleep habits. Daily calories and macronutrients will be calculated and used to provide dietary caloric goals during the 12-week TRE intervention.
2. **Time-Restricted Eating Protocol:** During the baseline visit, participants will meet with researchers and be informed of the intervention. They will be instructed to maintain a 6-8-hour eating window every day for 12 weeks after completion of the lead-in period. Participants will be allowed to self-select the timing of the eating window, but once selected, should attempt to maintain the schedule at a minimum 5 of 7 days per week for the duration of the study. Outside of that window, for the remaining 16-18 hours of day/night, participants will be asked not to consume calorie-containing food or drink. Beverages without calories, such as black coffee or tea, will be allowed. Participants will be instructed to consume plenty of water and electrolytes. Participants will also be provided a document with information about general healthy diet and exercise habits, in addition to instructions about the TRE protocol and a brief overview of each study visit..
3. **Daily Participant Tasks:**

*Meal Timing and Sleep Survey:* A daily electronic survey will be sent to each participant via text message or email, depending on participant preference, in the evening at 19:00 h. Participants will be asked to report the time of day they started and stopped eating, and their sleep habits and sleep quality from the previous night. Specifically, they will be asked to report their sleep duration, quality, and number/length of naps that day.

1. **Weekly Participant Tasks**:

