*Dietary Content Assessment:* Twice per week, participants will be asked to use the SnapCalorie^TM^ phone application to capture the meals eaten in a given day. At the baseline visit, participants will be instructed how to download and use the phone application. A text or email reminder will be sent in the morning at 08:00 h on the days that the participants are asked to record their meals. Using the application, participants will be asked to take photos of each meal and report estimated serving sizes. The application uses artificial intelligence technology to analyze meal composition which will be specifically used to estimate caloric content, and daily consumed fats, carbohydrates, and proteins.

*Weekly Survey:* Participants will be asked to complete a weekly survey to measure self-reported body weight, mood, and physical activity. The survey will be completed via Qualtrics. Researchers will send a reminder text or email each week with a link to the survey.

1. **Alternate Week Check-In:**

*Body Weight and Adverse Events Phone Call:* At the baseline visit, participants will be given a scale to measure at-home body weight. Every other week during the 12-week study, participants will be contacted by telephone to discuss at-home body weight changes and any adherence issues or adverse events.

Table 1. Study Visits and Detailed Procedures

|  |  | **Study Schedule** | | | | | | | | |
| --- | --- | --- | --- | --- | --- | --- | --- | --- | --- | --- |
| **Procedures** | | | **Pre-visit** | **Baseline Visit** | **Lead-in** | **Daily** | **Weekly** | **Weeks 2,4,6,8,10,12** | **Follow-up Visit** |  |
| Telephone Screening, Eligibility, and Consent | | | X |  |  |  |  |  |  |  |
| Survey Screening, Eligibility, and Consent | | | X |  |  |  |  |  |  |  |
| Montreal Cognitive Assessment | | |  | X |  |  |  |  | X |  |
| Consent | | |  | X |  |  |  |  |  |  |
| Pregnancy Test | | |  | X |  |  |  |  |  |  |
| In-Lab Questionnaire | | |  | X |  |  |  |  | X |  |
| Weight and Body Composition via BEI | | |  | X |  |  |  |  | X |  |
| Vital Signs | | |  | X |  |  |  |  | X |  |
| Venipuncture Blood Draw | | |  | X |  |  |  |  | X |  |
| UHDRS Assessment | | |  | X |  |  |  |  | X |  |
| Meal Timing and Sleep Survey | | |  |  | X | X |  |  |  |  |
| SnapCalorie^TM^ Meal Tracking | | |  |  | X |  | X |  |  |  |
| Body Weight, Mood, and Physical Activity Survey | | |  | X |  |  | X |  |  |  |
| Telephone Check-In | | |  |  |  |  |  | X |  |  |

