The primary safety outcome will be percent change in body weight and fat-free mass which will be examined using planned comparison paired t-tests between the baseline and follow-up visits. Differences in measures of vital signs, and safety labs will also be examined using planned comparison paired t-tests between the baseline and follow-up visits as additional safety measures.

Specific Aim 3: Explore whether TRE has beneficial effects on biomarkers of disease progression and behavioral, cognitive, and motor function outcomes using standard HD scales.

Differences in measures of blood biomarkers and UHDRS clinical scores will be examined using planned comparison paired t-tests between the baseline and follow-up visits.

Table 3. Statistical Analysis

| Measure | Statistical Test (for each measure) |
| --- | --- |
| Daily eating period (length of time) | Paired t-test from Baseline to Follow-up |
| Adherent days | Percent of days adherent to the TRE diet |
| Adverse events | Descriptive statistics |
| Body weight | Paired t-test from Baseline to Follow-up |
| Fat-free mass | Paired t-test from Baseline to Follow-up |
| Vital signs (Temp, BP, HR, RR, O2) | Paired t-test from Baseline to Follow-up |
| Safety labs (LFTs, Cr and BUN, CMP, A1c, BG, Lipids) | Paired t-test from Baseline to Follow-up |
| Biomarkers (NfL and GFAP) | Paired t-test from Baseline to Follow-up |
| UHDRS | Paired t-test from Baseline to Follow-up |
| Dietary composition | Descriptive statistics |
| Self-reported sleep habits | Descriptive statistics |
| Self-reported physical activity | Descriptive statistics |
| Mood | Descriptive statistics |

1. Sample Size, Expected Outcomes, and Translation of Results

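### TRE is explained, and a diet and exercise document probably handed over, before the lead-in meant to record normal habits, so the pre-TRE eating window and the calorie goals may rest on altered days

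*Protocol*

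**What the plan says.** The Study Design section of the protocol (section 4) fixes the order as baseline testing, then the lead-in, then TRE. Procedures Involved (section 6) gives the detail:

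- **Lead-in.** "During the 1-3 week lead-in period after the baseline visit", participants use the meal-photo application and the daily meal-timing and sleep survey to "log at least 7 days of their normal dietary and sleep habits".
- **Use of the lead-in.** "Daily calories and macronutrients will be calculated and used to provide dietary caloric goals during the 12-week TRE intervention".
- **Explanation of TRE.** "During the baseline visit, participants will meet with researchers and be informed of the intervention". The start is deferred: "They will be instructed to maintain a 6-8-hour eating window every day for 12 weeks after completion of the lead-in period".
- **Document.** Later in the same item: "Participants will also be provided a document with information about general healthy diet and exercise habits". It also carries TRE instructions and an outline of the visits. No date is given for handing it over.

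Table 1 marks the meal-timing survey under the lead-in and daily columns only, and under neither clinic visit. Table 3 lists daily eating period with a paired t-test from baseline to follow-up. It gives dietary composition descriptive statistics only.

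**The concern.** A run-in log is useful as a reference only if it captures what people do before the intervention touches them. Here the explanation of the eating window comes first, and general advice on diet and exercise appears to come with it. A participant could begin to tidy up meals, narrow the window or, in anticipation of fasting, eat more. Apart from the word normal and the later start date, nothing in the protocol asks participants to leave their habits alone during the lead-in.

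Two things hang on those days. The first is the pre-TRE eating window, which is needed to show how far TRE changed behaviour. The second is the calorie goals. These matter more, because the protocol names weight loss as its chief safety worry in this population, and a goal derived from untypical intake would stay in place through the TRE period.

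Separately, the eating-period test names two time points at which meal timing is not collected. No before-and-during comparison of intake is planned either, although intake is recorded in both periods.

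**Working it through.** The plan states no figure on this point, so there is none to reproduce. The check traces the order of events, then asks which results draw on the lead-in log.

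**Order of events (sections 4 and 6, Table 1).**
1. Baseline visit: clinic measurements, and TRE explained.
2. Lead-in of 1-3 weeks: at least 7 days logged.
3. TRE begins.

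The document's date is an inference. It sits in the item that opens with the baseline visit, is introduced by the word also, and Table 1 shows no other staff contact before TRE starts. However, goals calculated from the lead-in log can reach participants only after the log exists. Some later contact is therefore implied, even though Table 1 does not list it.

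**What depends on the lead-in log.**

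| Result | Source of the pre-TRE value | Depends on lead-in log? |
| --- | --- | --- |
| Weight, fat-free mass, vital signs, labs, NfL, GFAP, UHDRS | Baseline visit | No |
| Percent adherent days | Days under TRE only | No |
| Daily eating period (paired t-test) | Lead-in survey, the only scheduled one before TRE | Yes |
| Pre-TRE dietary composition | Lead-in application log | Yes |
| Calorie goals | Lead-in application log | Yes |

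**Size, by illustration only.** The protocol gives no habitual window and no habitual intake, so both are assumed.

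*Eating window.* Let H be the true habitual window, W the TRE window and d the narrowing during the lead-in. The true change is H − W, the observed change is H − d − W, and the relative error is d / (H − W).

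Take H = 12 h (assumed) and W = 8 h (the upper end of the protocol's 6-8 h), so the true change is 4 h:
- d = 0.5 h: observed 3.5 h, error 0.5/4 = 12.5%
- d = 1 h: observed 3.0 h, error 1/4 = 25%
- d = 2 h: observed 2.0 h, error 2/4 = 50%

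With W = 6 h the true change is 6 h, and the same drifts give 0.5/6 = 8.3%, 1/6 = 16.7% and 2/6 = 33.3%. If the window widened instead, the errors would have the same size with the opposite sign, and the change would be overstated.

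*Calorie goal.* Assume a habitual intake of 2000 kcal/day and a goal equal to logged intake. The protocol says only that the log is used to provide goals, so this equality is also an assumption. A lead-in shift of 5% to 10% moves the goal by 0.05 × 2000 = 100 to 0.10 × 2000 = 200 kcal/day. Over 12 × 7 = 84 days that is 8,400 to 16,800 kcal, in either direction.

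**Data available for a comparison.** Meal timing is surveyed daily in both periods. Intake is logged on at least 7 lead-in days and twice weekly under TRE, which is up to 2 × 12 = 24 days. A within-person comparison therefore needs no new data.

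**The case against.** The case against is substantial.

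- **Early change is not shown.** Participants are asked to log normal habits and told to start afterwards. This stands: the documents support a risk of unknown size and direction. A reader might infer that the lead-in days are already coached and that the delivered change is understated. The protocol does not establish that.
- **The document may be given later.** This stands as a possibility, because the calorie goals imply a contact after the log. It also means that fixing the date costs little.
- **The lead-in may not be the only evidence on prior eating.** A health behaviours survey is completed at baseline, and one exclusion criterion concerns recent TRE practice. The survey's items are not shown, and neither source is described as recording meal times. The lead-in remains the only scheduled meal-timing record before TRE.
- **Main outcomes are untouched.** This is correct, as the table of dependencies shows. A reader might infer that weight, laboratory or NfL results are biased by the sequence, but their baseline is measured at the visit itself.
- **Advice bundled with TRE confuses attribution.** A reader might conclude that changes in weight or NfL come from the diet and exercise advice. That is a general limit of a single-arm open-label pilot. Moving the document would not cure it, and it is not part of this point.
- **Baseline to follow-up may be shorthand, with averaging windows left to the SAP.** This is fair, and it keeps the Table 3 part small. The row as written still names visits without the data, and one line settles it.
- **A low goal would be noticed.** Weight is surveyed weekly and discussed by telephone every other week. That limits the consequence but does not restore the reference intake.
- **Face-to-face teaching has value, and consent discloses TRE anyway.** Both stand. The explanation should stay at the baseline visit, and some anticipation will remain.

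**Conclusion.** The point holds within narrow bounds. The protocol explains TRE, and probably supplies general diet and exercise advice, before the period intended to capture normal habits. Three things are exposed: the eating-window comparison, the description of pre-TRE diet, and the calorie goals. Every enrolled participant passes through this sequence, but whether any of them changes habits early cannot be known from the protocol. The illustrated errors (8.3% to 50% of the window change, 100 to 200 kcal/day in the goal) rest wholly on assumed habitual values and assumed shifts. They show scale only, and the sign could go either way.

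No sample size, power figure or clinic-based outcome is affected. The mismatch between Tables 1 and 3 on eating period is a matter of definition and needs correcting whether or not anyone changes behaviour. Describing intake without comparing it is permissible in a pilot, but it leaves unused a within-person comparison that the collected data would support.

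**What to change.** 1. Keep the face-to-face explanation of TRE at the baseline visit. State that the healthy diet and exercise document is sent only after the lead-in log is complete, together with the calorie goals, which must be communicated at that stage anyway. The outline of visits can be split off if it is wanted earlier.
2. Add an instruction at the baseline visit to keep eating and physical activity unchanged during the lead-in.
3. In Table 3, define the eating-period test as each participant's mean lead-in window against the mean window over the TRE weeks.
4. Add the same paired comparison, with a confidence interval, for mean daily energy and mean daily protein.

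**Cost.** One document goes out remotely 1-3 weeks later, and two analysis rows change. No visit, assay or participant is added. Some anticipation from the consent discussion and the explanation will remain, and photo-logging may itself affect eating. The lead-in will be a better reference but not a perfect one.

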**Table 2. Biomarker Analysis**

| **Primary Outcome Measures** | | | | |
| --- | --- | --- | --- | --- |
| **Biomarker** | **Definition** | **Measurement** | **Indication for Use** | **Method** |
| Neurofilament light protein (NfL) | A protein component of the neuronal cytoskeleton released into the CSF and blood from damaged neurons | A serum biomarker of neurodegeneration in HD, correlates with disease onset, stage, severity, and progression [26, 27] | Proof-of-concept measure of efficacy | ELISA or Single-molecule array (SIMOA) |
| Glial fibrillary acidic protein (GFAP) | A protein of astrocytes, increased in astroglial activation | A serum biomarker of neurodegeneration in HD, correlates with NfL, disease stage, and progression [28] | Proof-of-concept measure of efficacy | ELISA or Single-molecule array (SIMOA) |
| **Secondary Outcome Measures** | | | | |
| Peripheral mutant huntingtin protein (mHTT) | A protein known to play a critical role in the pathogenesis of HD | A leukocyte biomarker that correlates with HD severity, onset, and progression [29-31] | Exploratory mechanism of action measure | ELISA-based MSD |
| ULK1 | A mammalian serine/threonine protein kinase, plays a key role in the initial stages of autophagy | mRNA expression of ULK1 correlates with autophagic activity, potentially upregulated by TRE [32, 33] | Exploratory mechanism of action measure | qPCR |
| NRF2 | A transcription factor that regulates endogenous antioxidant response pathways | mRNA expression of NRF2 correlates with ROS response, upregulation has therapeutic indications in HD, potentially upregulated by TRE [34-36] | Exploratory mechanism of action measure | qPCR |
| Bioenergetic profile | A description of cellular energy metabolism characteristics | A measure of mitochondrial function and ETC activity, altered in HD, and potentially improved by TRE [37] | Exploratory mechanism of action measure | Seahorse analyzer |

7. Data and Specimens

- 1. Handling of Data and Specimens
     1. **Electronic Data Handling**: While the study is active, all PHI will be stored in a database housed on a secure OHSU server. PHI will be accessible to only investigators, and research staff listed on the protocol. No PHI will be stored or transferred via USB or other portable drives. We will obtain a waiver of the HIPPA authorization requirement for PHI collect at the time of the phone and survey screen.
        1. Research Electronic Data Capture (REDCap) and Qualtrics: Data and recruitment information for this project will be stored in OCTRI's installation of REDCap or Qualtrics, two highly secure and robust web-based research data collection and management systems. Features of REDCap that protect participants' privacy and data security include:

1. Physical Security: OCTRI's REDCap software is housed on servers located in ITG's Advanced Computing Center providing locked physical security
2. Electronic Security: The REDCap servers are housed behind both the OHSU firewall and a second ACC firewall.  All web-based data transmissions are encrypted with industry-standard SSL methods.
3. Controlled User Access: REDCap is employs a robust multi-level security system that enables researchers to easily implement "minimum necessary" data access for their research staff, including specification of data fields that are identifiers. This feature includes “single click” ability to provide completely deidentified (removing all identified data fields and shifting dates) for analysis or other purposes.  User activities are logged to enable auditing of all data access.   Access is integrated with OHSU's network such that users who are also OHSU employees are authenticated against their OHSU network credentials.
4. Data Integrity: REDCap is jointly managed in accordance with OHSU Information Security Directives by ACC staff and members of OCTRI's Biomedical Informatics Program, ensuring fidelity of database configuration and back-ups.  User activities are logged to enable auditing of all data changes.
   - 1. At the initial phone-screen, all participants will be assigned a unique code that will be used to identify them on documents residing outside of the secure database. Upon enrollment, participant study data will be recorded and stored in a password protected RedCap or Qualtrics database and will be identified only by the unique code assigned at the initial phone screen. Only persons listed on the IRB approved protocol will be given access to the databases.
     2. **Paper Data Handling:** All paper files (e.g. signed consent forms, participant sleep and meal timing diaries) will be stored in locked filing cabinets in restricted access offices at OHSU. Original records will be retained as the source document. Access to these files will be limited to study personnel listed on the IRB approved protocol.
     3. **Specimen Handling:** Blood samples will be identified only by the code assigned at the initial phone screen. Processing and handling of blood samples will be done by the OCTRI nursing and core lab staff. Samples will be stored and maintained by the [name] Lab -80 degree freezer. Access to study samples at OHSU will be limited to OCTRI core lab staff and study personnel listed on the IRB approved protocol. Coded biological samples may be sent to the Quanterix Corporation Laboratory for analysis.
   1. Sharing of Results with Subjects

With their consent, we will make known to the participant some of the information we have gathered from the physiological testing during the study. There is a chance that the study assessments and/or lab results will reveal some medical abnormality. This information will be conveyed to the participant, together with a recommendation to discuss the results with a physician if appropriate. All blood data collected and shared with participants is from a CLIA certified lab (OHSU).

- 1. Data and Specimen Banking

Venous blood samples will be stored for future research, which may include genetic research.

Samples will be hand carried by the study staff to the Hatfield Research Center and stored in secure freezers room for storage. Any remaining specimens after the required analyses have been conducted will be stored securely in the Hatfield Research Center. Samples may be shared with other investigators at OHSU or investigators outside of OHSU. All appropriate and required agreements will be in place prior to the release of samples. Samples will be identified by an assigned study participant ID number and will be transported by an approved courier. For any future use of these samples, IRB approval must be obtained. The repository guardian will be [name], who will be responsible for managing future access to these samples.

8. Data Analysis

The primary goals of this study are to assess if TRE in persons with premanifest and early manifest HD is 1) feasible, 2) safe, and 3) potentially efficacious.

Specific Aim 1: Examine the feasibility and tolerability of TRE for treating HD.

The percent of adherent days to the TRE intervention will be calculated and any adverse events will be recorded and described in detail.

Specific Aim 2: Evaluate the safety of TRE in premanifest and early manifest HD by measures of nutritional status.

The primary safety outcome will be percent change in body weight and fat-free mass which will be examined using planned comparison paired t-tests between the baseline and follow-up visits. Differences in measures of vital signs, and safety labs will also be examined using planned comparison paired t-tests between the baseline and follow-up visits as additional safety measures.

Specific Aim 3: Explore whether TRE has beneficial effects on biomarkers of disease progression and behavioral, cognitive, and motor function outcomes using standard HD scales.

Differences in measures of blood biomarkers and UHDRS clinical scores will be examined using planned comparison paired t-tests between the baseline and follow-up visits.

Table 3. Statistical Analysis

| Measure | Statistical Test (for each measure) |
| --- | --- |
| Daily eating period (length of time) | Paired t-test from Baseline to Follow-up |
| Adherent days | Percent of days adherent to the TRE diet |
| Adverse events | Descriptive statistics |
| Body weight | Paired t-test from Baseline to Follow-up |
| Fat-free mass | Paired t-test from Baseline to Follow-up |
| Vital signs (Temp, BP, HR, RR, O2) | Paired t-test from Baseline to Follow-up |
| Safety labs (LFTs, Cr and BUN, CMP, A1c, BG, Lipids) | Paired t-test from Baseline to Follow-up |
| Biomarkers (NfL and GFAP) | Paired t-test from Baseline to Follow-up |
| UHDRS | Paired t-test from Baseline to Follow-up |
| Dietary composition | Descriptive statistics |
| Self-reported sleep habits | Descriptive statistics |
| Self-reported physical activity | Descriptive statistics |
| Mood | Descriptive statistics |

1. Sample Size, Expected Outcomes, and Translation of Results

Aside from a single patient case report, an examination of TRE in persons with HD has never been explored. Thus, we must rely on existing data on TRE intervention in other populations. To detect differences in the percent change in body weight (Specific Aim 2) from baseline to follow-up, assuming a standard deviation of 2.4% from Gabel et al., we will have 95% power to detect a difference as low as 2.5% change in body weight in n=15 with two-sided Type I error of 0.05. To detect differences in plasma NfL (Specific Aim 3) from baseline to follow-up, assuming a standard deviation of 0.65 log pg/ml from Byrne et al., we will have 90% power to detect a difference as low as 15% in plasma NfL between baseline and follow-up in n=20 with two-sided Type I error of 0.05. *Thus, we will* *study 20 participants to maximize power while balancing feasibility* to derive meaningful proof-of-concept data.

9. Privacy, Confidentiality, and Data Security

Study staff will prepare and maintain complete and accurate study documentation in compliance with good clinical practice standards and applicable federal, state and local laws, rules and regulations. Specimens collected will include only a subject ID number and collection date on the collection and aliquot tubes. Data for this project, including demographics, medical and medication history, cognitive test results, and lab results will be stored in OCTRI's installation of REDCap, a highly secure and robust web-based research data collection and management system. Only researchers, including investigators and study coordinators, involved in this protocol will have access to the REDCap data. Paper files will be stored in restricted access offices in Sam Jackson Hall at OHSU, in locked offices contained within a key-code entry office suite.

10. Provisions to Monitor the Data to Ensure the Safety of Subjects

See *Data and Safety Monitoring Plan.*

11. Risks and Benefits

1. Risks to Subjects

*TRE Diet:* It is possible that participants will lose a small percent of body weight (not expected to be more than 2.5%) and it is expected to be primarily fat-mass. Participants may feel hungry during the fasting period and will be advised to stay properly hydrated to avoid feeling weak or light-headed.

*UHDRS Assessment:* The UHDRS clinical assessment requires attention and physical effort. Participants may experience minimal mental and/or physical fatigue.

*SnapCalorie^TM^ Phone Application:* The phone application participants will be asked to use twice per week is a commercially available service and we cannot guarantee data privacy or security through its use; however, personal information is not required and the only data that will be collected is of meal composition.

*Blood Draws:* There may be some discomfort or bruising on initial insertion of the needle into a vein.

*Survey Data:* Participants may be uncomfortable or feel concerned about answering survey questions about their personal sleep, mood, and health conditions. Surveys from this protocol may also not be generalizable outside of the English-speaking population.

1. Potential Benefits to Subjects

Although there will be no direct known physical benefit resulting from participation in this study, we will make known to the participant some of the information we have gathered throughout the study. There is a chance that the various samples taken during the study will reveal some medical abnormality. This information will be conveyed to the participant, together with a recommendation of a local clinic or physician from whom to seek treatment.

References

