Specific Aim 3: Analyze biomarkers of efficacy and explore whether TRE has beneficial effects on behavioral, cognitive, and motor function outcomes using standard HD clinical scales.

Hypothesis 3: We hypothesize that TRE will show trends toward improvements in biomarkers of HD progression and clinical measurements of these outcomes.

The aims will be accomplished by use of a 12-week prospective interventional open-label, single-arm trial that includes both field and in-laboratory data collection in persons with premanifest and early manifest HD. Specifically, participants will be asked to engage in a TRE diet, maintaining a 6-8-hour eating window every day for 13 weeks (+/- 1 week). A baseline (within 1-3 weeks of trial onset) and follow-up (within 7 days after week 12 of TRE) visit will assess body composition, safety labs, vital signs, clinical features of HD, and blood biomarkers. Participants will track the timing and content of diets, and record at-home body weight, physical activity, sleep, and mood using established survey techniques [11, 12].

*Primary endpoints: Feasibility, Safety, and Preliminary Efficacy*

Feasibility and tolerability: We expect that > 80% of subjects will adhere to the diet for the duration of the study with limited to no adverse events.

Body weight and fat-free mass: We expect that subjects will maintain their body weight and fat-free mass over the course of the 12-week study. Specifically, we hypothesize that at least 90% of subjects will have no more than a 10% loss in total body weight and no more than 5% loss in fat-free mass.

Vitals and blood chemistries: We expect that subjects will not experience adverse changes in vital signs, or measures of liver, kidney, or metabolic function.

Plasma neurofilament light protein (NfL) and Glial fibrillary acidic protein (GFAP): We expect that there will be an improvement in measures of plasma NfL and GFAP from baseline to follow-up.

*Secondary endpoints: Clinical Efficacy and Mechanism of Action*

Unified Huntington’s Disease Rating Scale (UHDRS) clinical assessment: We expect to see minor improvements in UHDRS motor, cognitive, independence, and functional capacity assessments; however, given the short-term nature of the study, it is unlikely significant changes will be observed.

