2. Diet Adherence and Sleep: A daily electronic survey will be sent to each participant via text message or email, depending on participant preference, in the evening at 19:00 h. Participants will be asked to report the time of day they started and stopped eating, and their sleep habits and sleep quality from the previous night.
3. Dietary Composition: Twice per week, participants will be asked to use the SnapCalorie^TM^ phone application to record the meals eaten in a given day. At the baseline visit, participants will be instructed how to download and use the phone application. A text or email reminder will be sent in the morning at 07:00 h on the days that the participants are asked to record their meals.
4. Weekly Survey: Participants will be asked to complete weekly surveys to measure self-reported body weight, mood, and physical activity. The survey will be completed via Qualtrics. Researchers will send reminder text messages each week with a link to the relevant survey.
5. Safety and Tolerability: At the baseline visit, participants will be given a scale to measure at-home body weight. Every other week during the 12-week study, participants will be contacted by telephone to assess at-home body weight and discuss adherence issues or any adverse events. If a participant loses more than 10% of their total body weight, they will be asked to stop the TRE diet and return to their prior dietary habits.

[figure not shown]

**Figure 1**. TRE in HD Study Design

5. Study Population

1. Number of Subjects

We will recruit 40 participants expecting roughly 25 participants to meet inclusion criteria with the goal of yielding a final sample of at least 20 in the experimental condition after a conservative expected level of attrition (~20%). These individuals will consist of males and females 21 years of age or older, with genetically confirmed premanifest or early manifest (stage I and II) HD defined by a CAP score greater than 368 or UHDRS TFC greater than or equal to 7, respectively. Subjects will be recruited from Oregon and Washington. See Statistical Analysis Section for justification of the selected sample size.

1. Inclusion and Exclusion Criteria

Inclusion Criteria

Subjects eligible to participate in this study are persons who:

1. Are of at least 21 years of age at Screening.

2. Must fulfill one of the following criteria:

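### The stated 90% power to detect a 15% change in plasma NfL with n=20 does not follow from the inputs the protocol gives

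*Protocol*

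**What the plan says.** The calculation is in Section 8 of the protocol, under the sample size heading. For NfL it works by "assuming a standard deviation of 0.65 log pg/ml", taken from a cited cohort analysis, and concludes that "we will have 90% power to detect a difference as low as 15% in plasma NfL between baseline and follow-up in n=20", with a two-sided type I error of 0.05. Table 3 gives the test: "Biomarkers (NfL and GFAP) | Paired t-test from Baseline to Follow-up".

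The sentence before it makes the corresponding claim for body weight. With an SD of 2.4%, "we will have 95% power to detect a difference as low as 2.5% change in body weight in n=15". The text then settles on 20 participants as a balance of power and feasibility. Section 5 arrives at the same number from recruitment: about 25 eligible, less roughly 20% attrition, leaves 20.

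Section 2 lists NfL together with GFAP among the primary endpoints, with the expectation "We expect that there will be an improvement in measures of plasma NfL and GFAP from baseline to follow-up". It names both again under the secondary endpoints. Table 2 classes both as primary outcome measures with a proof-of-concept purpose.

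The protocol does not state the base of the logarithm, whether 0.65 describes the within-person change or the spread between people, a baseline-to-follow-up correlation, or a mean NfL level.

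**The concern.** A 15% change is small on a log scale: about 0.16 natural-log units for a fall. Set against an SD of 0.65, it is a standardised effect of about a quarter of an SD. A paired t-test on 20 people needs about three-quarters of an SD for 90% power. The stated power and the stated inputs therefore disagree by a wide margin.

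This matters because NfL is one of the two biomarkers listed as primary, and the NfL sentence is the only power statement made at n=20. Section 5 sends the reader to this section for the justification of the sample size. Section 3 presents the study as groundwork for larger trials, whose planners would take from this sentence what a study of 20 can show about NfL.

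**Working it through.** **Inputs.** All are from Section 8: SD 0.65 log pg/ml; change 15%; n=20; two-sided alpha 0.05; paired t-test (Table 3).

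**Method.** For a paired t-test, d = (mean change)/(SD of change). Power comes from the non-central t distribution with n−1 degrees of freedom and non-centrality d√n.

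**Check on the protocol's own body-weight figure.** d = 2.5/2.4 = 1.042; non-centrality = 1.042 × √15 = 4.03; power = 96.3%. The protocol states 95%, so that claim reproduces when its SD is used directly as the SD of the change.

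**The same method for NfL, with 0.65 as the SD of the change.**

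| Reading of 15% | Change in log units | d | Power, n=20 |
|---|---|---|---|
| Fall, natural log | −ln 0.85 = 0.163 | 0.250 | 18.6% |
| Rise, natural log | ln 1.15 = 0.140 | 0.215 | 15.0% |
| 0.15 log units taken literally | 0.150 | 0.231 | 16.5% |
| Fall, base 10 | −log10 0.85 = 0.071 | 0.109 | 7.5% |
| Rise, base 10 | log10 1.15 = 0.061 | 0.093 | 6.8% |

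Other variants do not rescue the figure for a fall in natural logs: a one-sided test gives 28.6%, n=25 gives 22.5% and n=40 gives 33.8%.

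**What n=20 can detect with 90% power.** The required d is 0.764, so the change is 0.764 × 0.65 = 0.497 log units. In natural logs that is 1 − exp(−0.497) = 39% for a fall, or exp(0.497) − 1 = 64% for a rise. In base 10 the detectable fall is 1 − 10^(−0.497) = 68%. Conversely, a 15% fall with SD 0.65 (natural log) and 90% power would need 171 completers.

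**What would make the claim true (natural log).** The SD of change must be at most 0.163/0.764 = 0.213 for a fall, or 0.140/0.764 = 0.183 for a rise. If 0.65 is a between-person SD, then SD of change = 0.65 × √(2(1−r)), so r = 1 − (SD of change/0.65)²/2. This gives r = 0.947 for a fall and 0.960 for a rise. Power at other correlations:

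| r | SD of change | Power, 15% fall | Power, 15% rise |
|---|---|---|---|
| 0.5 | 0.650 | 18.6% | 15.0% |
| 0.8 | 0.411 | 38.9% | 30.3% |
| 0.9 | 0.291 | 66.0% | 53.2% |
| 0.95 | 0.206 | 91.8% | 82.2% |

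**The case against.** The strongest defence is that 0.65 may be a between-person SD. In a paired design, a biomarker that is stable within a person has a much smaller SD of change. At a correlation of 0.95, power for a 15% fall is 92%, so the trial may in fact be well powered. This stands as a limit on what can be concluded: a reader might infer that the true power is 19%, and the protocol does not support that, because it never says what 0.65 measures. The defence does not rescue the sentence, however. The 90% would then rest entirely on a correlation the protocol neither states nor sources, and at 0.8 or 0.9 it would still fail.

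A reader might also infer that the NfL calculation alone fixed the sample at 20. The text does not go that far. It cites feasibility alongside power, and Section 5 gives a recruitment and attrition argument that reaches the same number.

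It is tempting, too, to predict that a null NfL result would be taken as excluding a 15% effect. Nothing in the protocol commits to that. Hypothesis 3 speaks only of trends, the purpose is proof of concept, no decision rule depends on the NfL test, and participant safety is not affected.

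Finally, the 90% does come out if 15% is taken of a mean log value near 3.31 (0.15 × 3.31 = 0.497). That would explain the figure, but the protocol gives no mean, so it remains a guess. It would also describe a 39% fall in plasma NfL, not a 15% one.

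**Conclusion.** The claim of 90% power for a 15% change in NfL is unsupported as written. No reading of the stated inputs as a 15% change in plasma NfL comes near it, whatever the direction or log base, unless an undocumented correlation is added.

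The sizes are conditional. The 18.6% (fall), 15.0% (rise) and 39% detectable fall assume natural logs and 0.65 as the SD of the within-person change. That is the role the SD plays in the neighbouring body-weight calculation, which makes it the natural reading but not a stated one. If 0.65 is instead a between-person SD, power for a 15% fall runs from about 19% at r=0.5 to 92% at r=0.95. The failure of 90% to follow from the printed inputs does not depend on these assumptions; the exact true power does.

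**What to change.** Amend the NfL sentence in Section 8 in one of two ways.

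1. State the log base and the SD of the within-person log change (or the assumed correlation) with its source, and recompute the power from those.
2. Keep SD 0.65, identify it as the SD of the paired change in natural logs, and say that n=20 gives 90% power for a change of about 0.50 log units (about a 39% fall) and about 19% power for a 15% fall.

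The sample of 20 can remain. The text should then say that the body-weight calculation is already met at n=15 and that 20 is otherwise a feasibility choice. The body-weight calculation does not by itself explain 20.

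The cost is a change of wording and, unless a small SD of change can be sourced, a less favourable stated power. No extra participants or procedures are needed.
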